**Fig. 1 Fig1:**
[figure not shown]
Standard Protocol Items: Recommendations for Interventional Trials SPIRIT Figure. *cIMT* carotid intima media thickness; *CRF* cardiorespiratory fitness; *HDL* high-density lipoprotein; *SAAT* subcutaneous abdominal fat; *TG* triglycerides; *VAT* visceral abdominal fat

#### Participants and selection criteria

Participants will be recruited by pediatricians from the Pediatric Endocrinology Unit of the University Hospital of Txagorritxu and from primary care clinics (Vitoria-Gasteiz, Spain). Children aged between 8 and 12 years, meeting the international criteria for classification of T2D risk [1, 42], and having at least one parent or caregiver willing to participate in the program sessions, will be included (Table 1).

**Table 1 Tab1:** Eligibility criteria for the PREvention of DIabetes in KIDs (PREDIKID) study

Inclusion criteria
Aged 8–12 years
Criteria for the classification of risk of T2D [1]^a^
1. Obesity status according to the World Obesity Federation [24] 2. Overweight and the presence of at least one of the following metabolic abnormalities: 2.1. Family history of T2D in first- or second-degree relative; Signs of insulin resistance or conditions associated with insulin resistance (acanthosis nigricans, HOMA > 2.5, glucose between 100 and 125 mg/dL; Hypertension (systolic blood pressure ≥ 130 mmHg and/or diastolic blood pressure ≥ 85 mmHg); Dyslipidemia (HDL < 40 mg/dL, TG > 150 mg/dL); 2.2. Ethnic minority with higher risk
To have at least one parent or caregiver willing to participate in the program sessions
Exclusion criteria
Not available for assessment and intervention sessions
Medical conditions or medications that would affect study results or limit physical exercise

*PREDIKID* PREvention of DIabetes in Kids. ^a^According to the International Diabetes Federation [1]. *T2D* type-2 diabetes; *TG* triglycerides; *HDL* high-density lipoprotein; *HOMA* homeostatic model assessment

A pre-screening appointment will be scheduled with the investigation team to assess eligibility, family needs and commitment. Parents will provide the child’s and family health history and detailed contact information. After completion of the informed consent process, children will undergo anthropometric screening (height, body mass and waist circumference), complete physical examination and blood sampling, and will be selected for inclusion in the study if they meet the inclusion criteria (Table 1). Every child meeting the inclusion criteria will go through maximal exercise testing guarantee. Children with any medical condition that could affect the results of the study or that limits physical activity will be excluded.

#### Sample size calculation

Insulin resistance is the primary outcome of this study. We expect that pre-post intervention differences in our design consisting in two experimental groups, control and exercise group, will have a size effect (Cohen’s *d*) of 0.7 for insulin resistance (i.e., homeostatic model assessment, HOMA) (*N* = 34 in each group, 80% power and *α* of 0.05). These effect size estimates are based on previous studies performed in overweight children with similar age range and a with intervention programs including supervised exercise [33, 43, 44]. We observed in one previous study, in which the effect of the same intervention program was tested on hepatic fat in overweight/obese children, losses to follow-up of approximately 7% (data not shown). Previous studies have reported losses to follow-up of between 4 and 17%. Assuming a maximum loss of follow-up of 20%, we decided to recruit a total of 84 children (50% girls), 42 children for each group.

#### Randomization

Eligible participants will be randomly assigned after completing the baseline measurements to either the control group or the or exercise group (Fig. 2). Randomization of the participants into the control or exercise group will be done using Statistical Package for Social Sciences (IBM SPSS Statistics for Windows, version 21, Armonk, NY, USA) by an independent researcher. Assessment staff will be blinded to participant randomization assignment. Participants and their parents or guardians will be explicitly informed of the group to which they will be assigned, as well as of the study hypotheses. As exercise is potentially beneficial for the health of the children recruited in this trial, the waiting list control group strategy will be used, which means that the control group will receive the same exercise program when the post-intervention evaluations are finished.

**Fig. 2 Fig2:**
[figure not shown]
Planned study design

#### Family based healthy lifestyle education and psycho-educational intervention

Families in the control and the exercise groups will attend both the healthy lifestyle education and psycho-education program once every 2 weeks (11 sessions over 22 weeks) for 90 min (45 min in the healthy lifestyle education program and 45 min in the psycho-educational intervention). The design of the programs has been published elsewhere [45]. Briefly, the sessions of the healthy lifestyle education and psycho-educational interventions will be developed simultaneously and delivered to both parents (or caregivers) and children, separately.

The family based healthy lifestyle education program will be conducted by experienced nutritionists. The aim of the program will be in promoting changes in lifestyle behaviors strongly associated to obesity and T2D risk: promoting healthy dietary habits (reducing the intake of sugar, sugar-sweetened beverages and energy-dense foods, enhancing the daily consumption of fruits and vegetables, promoting breakfast and eating five meals/day), increasing regular physical activity levels, reducing time spent in sedentary behaviors and promoting sleep hygiene and adequate sleep duration.

The aims of the psycho-educational program will be to provide parental skills to optimize the family environment in order to make positive changes in their lifestyles and to learn assertive communication skills. The program will also provide skills to children for managing the emotions and feelings that they are experiencing and to improve their self-esteem and psychological wellbeing.

#### Exercise training intervention

The exercise group will do exercise 3 days/week, 90 min per session, over a 22-week period. The program will be open to the families 5 days per week to choose a total of 3 days/week. Sessions will be designed and supervised by exercise specialists. The design of the exercise program has been published elsewhere [45]. Briefly, the program consists of cardiovascular endurance (60 min) and muscle strength exercises (10 min). The sessions also include 10 min of warm-up period, 5 min for giving instructions and 5 min of cool-down period at the end, consisting mainly of stretching exercises. Moderate to vigorous intensity aerobic workout is the main part of the exercise session (60 min) and consists of games, circuits and start-and-stop activities. The emphasis of the program is on intensity doing special emphasis on high intensity activities (above 75% of maximal heart rate (HRmax) obtained from either the cardiopulmonary exercise test in the laboratory or the 20-m shuttle run test) and enjoyment. Participants will wear a heart rate monitor (Polar RS300X) during the exercise sessions to ensure achievement of the target heart rate zone. Heart rate monitors will be programmed according to individual percentage of HRmax as follows: (1) very light intensity: from 50 to 57% of HRmax, (2) light intensity: from >57 to 64% of HRmax, (3) moderate intensity, from >64 to 76% HRmax, (4) high intensity or vigorous: from >76 to 96% HRmax and (5) maximal intensity: > 96% of HRmax.

### Participant retention and adherence

The success of the intervention is strongly dependent on enjoyment and active participation. In order to motivate children’s active participation, the staff will use several strategies to celebrate success achieving the proposed objectives in both the healthy lifestyle education and the exercise programs: celebrate and recognize their efforts, reward with smiley emoticons, etc. Children who complete the program successfully will be rewarded with a certificate of completion. The attendance to the lifestyle education and psycho-education programs and of the exercise program will be recorded. Children will be marked as absent when: (1) the child does not attend the exercise session or does not participate in the proposed activities and (2) the child and at least one parent/caregiver do not attend one session of the healthy lifestyle education and psycho-educational programs.

### Outcome measures for the first objective

IRS and the risk of T2D is characterized by excess adiposity, low levels of insulin sensitivity, dyslipidemia and hypertension. In the current project, the primary outcome is insulin resistance. Secondary outcome variables include total, abdominal and visceral adiposity, ectopic fat (hepatic and pancreatic fat), cardiorespiratory fitness, cardiovascular disease risk factors and inflammation markers, hepatokines and adipokines (Table 2). Primary and secondary outcomes will be evaluated at baseline and repeated after 22 weeks of intervention (Fig. 2). Post-intervention measurements will be scheduled within 3 days following the last healthy lifestyle program session or exercise session in the control or in the exercise group, respectively.

**Table 2 Tab2:** Summary of the methodology of primary and secondary outcome measurements and potential confounders in the PREvention of DIabetes in KIDs (PREDIKID) study

Measure	Methodology
Primary outcomes	
Insulin resistance	Homeostatic model assessment (HOMA), biochemical analyses
Expression of miRNA in circulating exosomes and white blood cells	RNA-seq methodology
Secondary outcomes	
Physical measures	
Body mass (kg)	Scale
Height (cm)	Stadiometer
Waist circumference (cm)	Non-elastic tape
Blood pressure (mmHg)	Oscillometric monitor device
Body fat (%)	Dual X-ray absorptiometry
Abdominal adiposity (g)	Dual X-ray absorptiometry
Visceral abdominal adiposity (cm^2^)	Magnetic resonance imaging
Hepatic fat (%)	Magnetic resonance imaging
Pancreatic fat (%)	Magnetic resonance imaging
Carotid intima medial thickness (mm)	Doppler ultrasonography
Biochemical measures	
Glucose (mg/dL)	Enzymatic spectrophotometry
Insulin, leptin, adiponectine, fetuin-A, FGF21	Enzyme-Linked Immunosorbent Assay
Hemoglobin A1c	Enzymatic tests
Total cholesterol, HDL- and LDL-cholesterol (mg/dL)	Enzymatic spectrophotometry
Triglycerides (mg/dL)	Enzymatic spectrophotometry
Alanine aminotransferase (U/L)	Enzymatic tests
Aspartate aminotransferase (U/L)	Enzymatic tests
Gamma glutamyl transferase (U/L)	Enzymatic tests
C-reactive protein (g/dL)	Enzyme immunoassay
TSH, T3, T4	Radioimmunoassay
Uric acid (mg/dL)	Enzymatic spectrophotometry
Urea, bilirubin	Enzymatic spectrophotometry
Cardiorespiratory fitness	20-m shuttle run test Cardiopulmonary exercise test
Dietary assessment	24-h recalls and food frequency questionnaires
Physical activity assessment	Accelerometry and questionnaires
Sleeping habits	Accelerometry and questionnaires
Sedentary behaviors	Questionnaires
Potential confounders	
Pubertal development (Tanner stage)	Physical examination
Sociodemographic variables	
Socioeconomic status	Questionnaires
Neonatal variables	Health booklets and questionnaires
Family medical history	Questionnaires
Demographic characteristics	Questionnaires

*PREDIKID* Prevention of Diabetes in Kids; *FGF21* fibroblast growth factor 21; *HDL* high-density lipoprotein; *LDL* low-density lipoprotein; *miRNA* micro RNA; *TSH* thyroid stimulating hormone; *T3* triiodothyronine; *T4* free thyroxine

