## Methods

### Design

The PREvention of DIabetes in KIDs (PREDIKID) study is a randomized clinical trial (RCT) (ClinicalTrials.gov, ID: NCT03027726) (see Additional file 1 and Fig. 1 for the associated Standard Protocol Items: Recommendations for Interventional Trials (SPIRIT) Checklist and Figure, respectively). Children will be randomly allocated to the control group or the exercise group and will be followed for 22 weeks. All the families included in the study will participate in a lifestyle education and psycho-educational program conducted by a multidisciplinary team of health care professionals (physicians, nutritionists and dieticians, psychologists and exercise specialist) and scientists. As both groups will receive the same lifestyle education and psycho-education program, differences in changes in outcome variables will be due to the additional effect of the exercise intervention. This study was reviewed and approved by the Ethics Committee of Clinical Investigation of Euskadi. All parents or legal guardians will sign an informed written consent and all the children will give their assent before being enrolled in the study. The informed consent will be obtained by the pediatricians participating in the recruitment.

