##### Physical activity, sedentary behavior, dietary assessment and sleep

We will assess all these lifestyle behaviors both at the beginning and the end of the intervention. Children will wear an accelerometer on the non-dominant wrist (ActiSleep, Actigraph, Pensacola, FL, USA) for seven consecutive days for 24 h to record physical activity intensity levels and patterns, as well as sleeping habits and participants will also complete a diary log. Sedentary behaviors, such as watching TV, playing computer games, playing video games or phone games and surfing the Internet, will be self-reported by the children using validated questionnaires [66]. Dietary intake will be evaluated by two non-consecutive 24-h recalls within a period of 7 days by nutritionists and a self-reported semi-quantitative food frequency questionnaire.

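### The post-intervention visit is timed from a different event in each arm with no minimum interval since exercise, so the HOMA contrast cannot separate a last-session effect from the effect of 22 weeks of training

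*Protocol article*

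**What the plan says.** Under Outcome measures for the first objective, the protocol article gives a nominal time point for both arms: "Primary and secondary outcomes will be evaluated at baseline and repeated after 22 weeks of intervention". The next sentence turns this into a scheduling rule, with measurements booked "within 3 days following the last healthy lifestyle program session or exercise session in the control or in the exercise group, respectively". The closing word of that rule assigns the lifestyle session to controls and the exercise session to the exercise arm.

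The two programmes run on different schedules. Families in both arms attend the lifestyle and psycho-educational sessions "once every 2 weeks (11 sessions over 22 weeks) for 90 min". For the exercise arm alone, "The exercise group will do exercise 3 days/week, 90 min per session, over a 22-week period", and families pick their days: "The program will be open to the families 5 days per week to choose a total of 3 days/week".

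The primary outcome is HOMA, from a fasting venous sample. Randomisation follows the baseline measurements. The Data analyses plan tests the time-by-group interaction in a repeated-measures analysis of variance under intention to treat. The Design section states how the result will be read: "differences in changes in outcome variables will be due to the additional effect of the exercise intervention".

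**The concern.** The sample behind the primary outcome is taken under conditions that differ by arm. In the exercise arm it follows a supervised session by at most 3 days and possibly by one. In the control arm it follows an education session. If a single session lowers fasting insulin or glucose for a short time, that change enters the between-arm difference and cannot be told apart from the result of 22 weeks of training. Blinding the assessors does not help, because the child's state differs and not the way it is measured.

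What is at stake is interpretation. The Discussion presents the programme as a possible preventive model for type-2 diabetes. A reader will take the HOMA difference as evidence of a training effect that outlasts the latest session, and the schedule as written cannot show how much of it does.

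**Working it through.** **1. The plan's own figure.** Inputs from Sample size calculation: d = 0.7, 80% power, alpha 0.05 (two-sided assumed, as the article does not say), 34 per arm.

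- Normal approximation: n = 2(1.960 + 0.842)²/0.7² = 32.04, rounded up to 33 per arm.
- t-based solution: 33.02, rounded up to 34. Power at 34 per arm is 81%.

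The stated 34 reproduces, and this point does not alter it.

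**2. Can the planned analysis remove a last-session effect?** Write L for the lasting training effect and S for any short-lived effect of the last session.

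- Exercise arm, post minus baseline: common change + L + S.
- Control arm, post minus baseline: common change.
- Time-by-group interaction: L + S.

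Baseline is measured before allocation, so it carries no programme session in either arm and does not cancel S. The stated model has no term for time since the last session. The trial therefore estimates the sum only.

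**3. What S could do.** The documents give neither its size nor its duration, so the values of S below are assumed for illustration (two-sample t test, 34 per arm).

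| Assumed S (SD) | Share of d = 0.7 | Chance of a significant result if L = 0 | L if L + S = 0.7 | Power for that L alone |
|---|---|---|---|---|
| 0 | 0% | 5% | 0.7 | 81% |
| 0.1 | 14% | 6.9% | 0.6 | 68% |
| 0.2 | 29% | 12.8% | 0.5 | 53% |
| 0.3 | 43% | 23.0% | 0.4 | 37% |
| 0.4 | 57% | 36.9% | 0.3 | 23% |

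The share is S/0.7; for example 0.1/0.7 = 14% and 0.3/0.7 = 43%.

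**4. Calendar time.** Eleven sessions at 14-day spacing span 10 × 14 = 140 days; 22 weeks are 22 × 7 = 154 days. The control anchor can fall up to 154 − 140 = 14 days before the end of week 22. If the last lifestyle session is held in week 22, the gap is about nil. The article does not say which.

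**5. Usual spacing of exercise.** Three sessions a week average 7/3 = 2.3 days apart. A child still in the programme is therefore usually within about 3 days of a session.

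**The case against.** The strongest reply is about the estimand. The stated aim is the effect of a 22-week programme that includes supervised exercise, against the same programme without it. Nowhere does the article promise an effect measured after exercise has worn off. At an average spacing of 2.3 days, a sample within 3 days of a session reflects the normal state of a child in the programme. This stands: randomisation supports the contrast for the programme as delivered. It does not settle how much of the difference is training, which is what a prevention claim needs.

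The size is also unsupported, and that stands too. The documents give no last-session effect on HOMA, and zero lies within the assumed range. The earlier trials behind d = 0.7 may have sampled soon after exercise themselves; their timing cannot be seen here.

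A reader might infer more than the text bears:

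- **No common time point.** The sentence before the scheduling rule says 22 weeks for both arms. What is missing is one window that applies this to both arms.
- **Controls assessed earlier.** The lag could reach about two weeks or be nil.
- **No usable visit date for a child who stops attending.** This holds only if the last session means the last one that child attended. It can equally mean the final scheduled session.
- **A contradiction with the lifestyle measures.** Accelerometers are worn "for seven consecutive days for 24 h to record physical activity intensity levels and patterns", and "Dietary intake will be evaluated by two non-consecutive 24-h recalls within a period of 7 days by nutritionists". These conflict with the 3-day rule only if scheduling means completion. It may mean the start, and the section on these behaviours gives its own timing.

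An article may also leave sampling order and rest intervals to the full protocol. That covers the missing minimum interval taken alone, but not the stated rule that uses a different anchor in each arm.

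**Conclusion.** The point holds as a limit on interpretation. The stated rule lets the fasting sample follow a supervised session by as little as a day in one arm only, and neither the baseline nor the planned analysis separates that session's effect from 22 weeks of training. The Design section's attribution is sound if the exercise intervention is taken to include its most recent session. It is not established for a lasting training effect.

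The size is unknown. The illustrative 14% to 43% rests wholly on an assumed 0.1 to 0.3 SD and on 34 evaluable children per arm. A reader might conclude that the primary comparison is invalid or that its type I error is inflated. The documents do not support this: for the programme as delivered the test keeps its level, and the higher rejection rates in the table apply only to a claim about the lasting part. This is a cheap improvement and not an error that must be corrected before the trial can be interpreted.

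**What to change.** Replace the arm-specific anchors with one rule:

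- Define a single week-22 visit window for every randomised child, counted from randomisation or programme start (about day 154) and independent of attendance.
- Take the fasting sample after the same pre-specified minimum exercise-free interval in both arms, inside the present 3-day limit, and before maximal exercise testing. The documents give no basis for a particular length, so the investigators should choose and justify it.
- Record time since last exercise for every child and use it in a sensitivity analysis. This can only be partial, because supervised sessions occur in one arm and time since the last one is not randomised.
- State that 7-day accelerometry and the dietary recalls have their own window, the same in both arms.

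The cost is wording, scheduling and less flexible appointments. Recruitment began in March 2017, so the first children could reach week 22 around the August 2017 publication. If some have already been assessed under the present rule, two timing rules will coexist. Record which rule applied to each child, with time since last exercise where it can be recovered, and report both.

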#### Primary outcome measure: insulin resistance

HOMA has been shown to be the more reliable method to assess insulin resistance in children [46]. The computer-generated HOMA will be used [47].

#### Secondary outcomes

##### Anthropometry and blood pressure

Body mass (SECA 760), height (SECA 220) and waist circumference (SECA 200) will be measured following standard protocols at least twice until consistent measures are obtained and, thereafter, Body Mass Index (BMI) and waist to height ratio will be calculated. Systolic and diastolic blood pressure measurements will be performed following the recommendations for children [48] using an arm blood pressure oscillometric monitor device (OMRON® M6).

##### Total, abdominal and visceral adiposity

In children, the role of total, abdominal and visceral fat accumulation in the development of IRS, and ultimately T2D, is well established. One recent report observed that every additional 1% of adiposity at 8–10 years decreased insulin sensitivity by 2.9% 2 years later [22]. Total and abdominal adiposity will be measured by dual energy X-ray absorptiometry (HOLOGIC, QDR 4500 W). Visceral adiposity will be measured by magnetic resonance imaging using a 1.5-T system (MAGNETOM Avanto, Siemens Healthcare, Erlangen, Germany) equipped with a phased-array surface coil and a spine array coil. Automated visceral fat measurement will be achieved by image processing (Matlab, Matworks Inc., Natick, MA, USA).

